### **Study Intervention Rationale**

The rationale for VentFirst can be summarized as follows (with details provided below):

- 1) Delayed cord clamping has been shown to be beneficial in preterm infants that are spontaneously breathing
- 2) If infants are not breathing well, most providers feel it is necessary to clamp the cord early so as not to delay resuscitation by the neonatology team.

- 3) Many EPT infants do not breathe well, so are not able to benefit from DCC
- 4) If assisted ventilation were provided during DCC, more EPT infants could benefit from the extra time attached to the placenta.
- 5) Potentially even more importantly, assisting ventilation during DCC may lead to a smoother cardiovascular transition. Preclinical studies have shown that achieving lung inflation prior to cord clamping stabilizes the blood pressure, heart rate, and cerebral blood flow and oxygenation, compared to cord clamping before lung inflation. If this is the case in humans, then IVH risk could be lower with assisted ventilation prior to cord clamping.

### **Rationale for Delayed Cord Clamping (DCC): Clinical Studies**

Multiple small randomized clinical trials of DCC for preterm infants have been published, showing some advantages and low risk. In a meta-analysis of 14 studies of delayed (30-180 sec) compared to immediate/early (~15 sec) clamping for preterm infants, advantages of DCC included a higher hematocrit, less need for blood transfusion, less need for vasopressor administration, and a lower incidence of intraventricular hemorrhage (IVH) and necrotizing enterocolitis.

With regard to disadvantages, it was previously thought that DCC might lead to hypothermia, polycythemia, hyperbilirubinemia, and delayed resuscitation. However, hypothermia and polycythemia were not found to be significant problems in randomized clinical trials, and bilirubin was higher and duration of phototherapy longer in some but not all studies.

Whether DCC resulted in delayed resuscitation could not be assessed in these studies because in most cases if a baby was judged to require resuscitation the team disregarded the study assignment and clamped the cord early.

### **Rationale for Assisted Ventilation prior to Cord Clamping: Preclinical Studies**

Many EPT infants do not breathe well on their own immediately after birth, and their umbilical cord is clamped before their lungs are inflated. This puts them at a significant disadvantage physiologically. When the umbilical cord is cut and the placental circulation removed before the

lungs are inflated, the following adverse transition occurs: 1) blood return from placenta to right atrium (a major component of cardiac preload) abruptly ceases 2) pulmonary vascular resistance remains elevated and blood bypasses the fluid-filled lungs shunting right to left through the ductus arteriosus 3) the under filled left ventricle pumps against high systemic vascular resistance (rather than to the low resistance placenta), compromising cardiac output.

Recent evidence in preterm animal models suggests that inflating the lungs prior to cord clamping is beneficial. Lambs delivered at the equivalent of 28 weeks of human gestation either had the umbilical cord clamped immediately and assisted ventilation provided after, or had assisted ventilation prior to cord clamping. Lambs in the “Clamp First” group had significant decline in heart rate and oxygenation and swings in cerebral blood flow compared to lambs in the “Vent First” group that had more stable cardiovascular and cerebral blood flow parameters. In extremely preterm infants, rapid changes in cerebral blood pressure and flow if the cord is cut before the lungs are inflated may lead to ischemic injury or intraventricular hemorrhage. Since many EPT infants do not breathe well on their own immediately after birth, the goal of the VentFirst RCT is to test whether providing ventilatory assistance during DCC reduces IVH and other common morbidities of EPT infants.

### **Rationale for Study Design**

VentFirst is a randomized clinical trial of a delivery room intervention for EPT infants with the goal of reducing IVH, a major complication of EPT birth. Infants randomized to the Standard Arm will receive current standard practice for EPT infants, as recommended by ACOG in 2012, of 30-60 sec DCC. Cord clamping at 30 sec if not breathing well and 60 sec if breathing well has been suggested; however, given recent shifts in clinical practice, it is at the discretion of the OB and Neonatology teams to delay cord clamping past 30 seconds, but not longer than 60 seconds, even if the baby is not breathing well. Standard Arm infants will receive assistance with ventilation after the cord is clamped. Infants randomized to the VentFirst Arm will receive assisted ventilation from 30-120 sec after birth, while attached by the umbilical cord to the placenta. The cord will be clamped at 120 sec after birth. Both groups will get standard breathing assistance and other resuscitation measures, the only difference being timing of cord clamping and timing and location of beginning assisted ventilation. In both groups, initial assisted ventilation will be either CPAP (continuous positive

airway pressure) via face mask if the EPT infant is breathing or PPV (positive pressure ventilation) via face mask if the infant is not breathing well. Endotracheal intubation will be performed as per standard NRP guidelines if the infant is not responding to PPV via face mask. Per protocol, intubation will not be performed until after cord clamping (although the lead neonatologist present may elect to clamp the cord early, should intubation be felt to be emergently indicated before the 120-second delay prescribed by protocol).

The study was designed primarily to determine whether EPT infants not breathing well on their own will benefit from assisted ventilation during prolonged placental transfusion. Infants breathing well on their own might also benefit from assisted ventilation and extra time attached to the placenta before cord clamping, but we expect this effect to be smaller.

Of note, infants randomized to the “Standard” group will be getting 30-60 seconds of DCC, which is within the range of previous clinical trials and is the current recommendation from ACOG. It is not known whether 120 sec of DCC is more beneficial than 30-60 sec. This would not be feasible to study for this population, since most practitioners would not accept delaying resuscitation of non-breathing EPT infants for 120 seconds during DCC.

The study intervention cannot be blinded but the primary outcome will be assigned by expert radiologists at non-study institutions who will be blinded to study arm.

## 2 STUDY OBJECTIVES

### 2.1 Hypotheses

- 1) Extremely preterm infants (EPT, 230/7 to 286/7 weeks' gestational age) **not breathing well** by 30 seconds from birth are less likely to have IVH on head ultrasound 7-10 days from birth if they receive assisted ventilation from 30 to 120 seconds followed by cord clamping, compared to those with cords clamped at 30-60 seconds, followed by assisted ventilation.
- 2) EPT infants **breathing well** by 30 seconds from birth are less likely to have IVH on head ultrasound 7-10 days from birth if they receive assisted ventilation from 30 to 120 seconds followed by cord clamping, compared to those with cords clamped at 30-60 seconds, followed by assisted ventilation.

### 2.2 Specific Aim

Conduct a randomized clinical trial to test the above two hypotheses to facilitate development of the following guidelines for resuscitation of EPT infants at birth:

*If both hypotheses are supported:* All EPT infants should have DCC for 120 seconds, with assisted ventilation provided prior to cord clamping.

*If hypothesis 1 is supported, but hypothesis 2 is not:* All EPT infants should have DCC for at least 30 seconds, and if the infant is *not breathing* by 30 seconds, assisted ventilation should be provided while the cord remains un-clamped until 120 seconds after birth.

*If both hypotheses are refuted:* All EPT infants should have DCC for at least 30 seconds (based on previous studies), but there is insufficient evidence to recommend more prolonged DCC with assisted ventilation for those not breathing well at 30 seconds.

### 3 SUBJECT ELIGIBILITY

Infants born at participating sites who fulfill the inclusion and exclusion criteria listed below are eligible for enrollment in this study. Mothers of all races and ethnicities will be approached for consent. Maternal written informed consent will be obtained prior to delivery.

#### **Inclusion Criteria (All inclusion criteria MUST be present)**

- [1] 230/7 – 286/7 weeks gestation at delivery
- [2] Written informed consent obtained before delivery

#### **Exclusion Criteria (All exclusion criteria MUST NOT be present)**

- [1] Life threatening condition of fetus (including but not limited to: severe hydrops, lethal chromosomal abnormality, severe congenital malformation)
- [2] Suspected severe fetal anemia
- [3] Monochorionic twins
- [4] Multiple gestation greater than twins
- [5] Decision made for comfort care only
- [6] Medical emergency necessitating emergency delivery (e.g., complete placental abruption)
- [7] Obstetrician or Neonatology concerns for inappropriateness of the study intervention based on other maternal or fetal factors (must specify reason on the screening log)

#### **Twins**

**Centers may consider enrolling twins once they have completed the VentFirst intervention on at least 3 singleton C-section Vent First deliveries**, in order to gain experience with setting up and carrying out the VentFirst protocol. At that point, the site PI and site Obstetrician can opt to begin approaching **mothers of twins (dichorionic only)** about participation in the study. Team training on logistics of twin VentFirst deliveries should be carried out prior to randomizing any twin gestations. The site PI or site Obstetrician may opt to not enroll twins.

## 4 TREATMENT PLAN

### Study Overview

This is a multicenter, randomized, phase III clinical trial that will randomize 940 EPT infants into one of two study arms, stratified by gestational age (230/7 – 256/7 weeks and 260/7 - 286/7 weeks):

- 1) **Standard Arm** with delayed cord clamping at 30-60 seconds and assisted ventilation provided after cord clamping
- 2) **VentFirst Arm** with delayed cord clamping at 120 seconds and assisted ventilation provided before cord clamping.

The study intervention will occur in the first 2 minutes after birth. Initial assisted ventilation in both groups will consist of application of continuous positive airway pressure (CPAP) or positive pressure ventilation (PPV) via face mask. Study data will be collected in the delivery room and from the infant's medical record from birth until 36 weeks postmenstrual age (PMA = gestational age at birth + age from birth) or until discharge home, whichever comes first. Maternal data will be collected from the mother's chart until her hospital discharge after delivery. If an infant is transferred to an outside facility prior to 36 weeks PMA, a member of the study team will follow-up with the outside facility regarding outcomes to 36 weeks PMA. Permission to contact the outside facility will be obtained from the mother prior to conducting this follow-up.

The study is being conducted at 12 sites in the United States and Canada. It is expected that accrual will take place over 5 years.

### Screening

At each site, medical records of women hospitalized and expected to deliver at 230/7- 286/7 weeks gestation will be reviewed by a member of the study team for study eligibility.

After medical record review, if *all* of the inclusion criteria and *none* of the exclusion criteria are met, the mother will be approached by a member of the study team to provide consent for herself and her infant to participate in the study. A study consent video might be available to help explain the study. The video would be approved by each sites' IRB and would NOT replace the written informed consent process.

There may be occasions where a mother signs consent and then is discharged home prior to delivery. At readmission, a member of the study

team must confirm that all study inclusion criteria are *met* and all exclusion criteria *not met* prior to randomization.

### **Enrollment**

Once informed consent is obtained, the mother-infant dyad is considered enrolled in the study. The following registration data will be entered into the study database (MuSIC, Multi-Schema Information Capture):

- Registering site and investigator
- Date of signed informed consent
- Mother's demographic data
- Estimated gestational age of the fetus
- Documentation of study eligibility

Detailed instructions for the registration process can be found in the study Manual of Procedures (MOP).

### **Randomization**

Study eligibility and consent must be confirmed prior to randomization.

Randomization should be done as close to the expected time of delivery as possible, preferably within one hour. At each site, randomization will be done by the Clinical Research Coordinator (CRC) or a trained member of the study team via a web-based platform.

The CRC or trained team member will login to the randomization module, enter the current estimated gestational age, and request a study arm assignment. The server will provide the arm assignment based on a randomization scheme specified by the project biostatistician along with a single use alphanumeric transaction identifier consisting of a color and a 2-digit number, such as "red51." The server will display the transaction identifier, site code, transaction time, gestational age and arm assignment to the requesting personnel.

A delivery room script specific to the study arm "Standard 30-60 second" or "VentFirst-120 second" will be available to the neonatology team attending the delivery. The transaction identifier must be recorded on the appropriate delivery script.

**Twins will automatically be assigned to the same study intervention and will have the same transaction identifier but will be assigned a unique subject number in the MuSIC database.**

## **Delivery Room Study Intervention**

### **VentFirst Team Roles**

VentFirst deliveries will be attended by NRP-trained neonatology providers who usually attend EPT births. This typically includes some combination of a neonatology attending physician, neonatology fellow physician, and/or Neonatal Nurse Practitioner. Providers will be trained in the VentFirst protocol using computer-based learning modules, training videos, and simulation sessions with regular updates as specified in the MOP.

For infants randomized to the VentFirst arm, a trained and NRP-certified neonatology provider will be assigned to carry out the 2-minute intervention after birth.

A VentFirst Facilitator (VFF) will be assigned after randomization and before delivery. This individual will have a clipboard with a script and a timer and will be responsible for timing the interventions and reading the protocol script from birth to 120 seconds. The VFF will also write DR data on the VF Script. An audio recorder may also be used for quality control to confirm timing of interventions. The site CRC and PI may use the audio recordings to review the data written on the DR script by the VFF. Audio recordings will be identified by subject ID, stored in a secure location at each site for quality control review, and made available to the UVA study team during site audits if needed.

### **Delivery Preparation**

- If randomization is to the VentFirst Arm and delivery is by Cesarean section, a neonatology provider will be sterilely scrubbed and dressed to enter the operating field. Equipment needed for assisting ventilation that might contact the sterile field will be sterilized or placed in a sterile wrap, or will be single use removed from company packaging immediately before delivery when sterilization is not feasible. The Fisher & Paykel company (F&P) has agreed to provide a gas-sterilized version of their standard masks and tubing for delivering CPAP and/or positive pressure ventilation to study subjects who are being delivered by Cesarean section. However, since the sterile packaging is not yet commercially available, F&P will package the standard sterilized equipment in specially-labeled packaging and require that the equipment be used for VentFirst study subjects only. VentFirst sites can opt to use the sterilized masks provided by (F&P) if they choose.

- Equipment for providing CPAP and PPV, oxygen and air tanks and blender, and flowmeter which are standard for resuscitation of EPT infants will be on a mobile stand for deliveries randomized to VentFirst resuscitation prior to cord clamping. See the study MOP for VentFirst equipment configuration requirements and instructions.
- A VFF will be assigned to record time of birth and will read the VentFirst delivery script which gives instructions for the respective arm and will record basic delivery room data on the DR script (See MOP for the delivery script). The VFF will record the number of seconds after birth that the cord was clamped and, if the time is more than 15 seconds shorter or longer than the assigned time, will record the reason for this variance. An audio recorder may be activated prior to delivery and the audio tape may be reviewed by the CRC or site PI after delivery to verify data written on the DR script.

### **At Delivery**

#### **Initial Steps (both arms)**

- For **vaginal** deliveries, the infant will be placed on a stable surface near the introitus on a warming pad with OB towel and/or plastic drape to prevent hypothermia.
- For **Cesarean section** deliveries, the infant will be placed on the mother's pelvis or a suitable stable surface on a sterilely covered warming pad and sterile OB towel and/or sterile plastic drape.
- A heart rate monitor may be applied.
- The infant will be stimulated to breathe for up to 30 seconds from birth, including bulb suctioning of the mouth and nose if indicated.
- At 20 seconds from birth, the VFF will announce "20 seconds; Neo assess breathing. Is the baby breathing well or not?" The neonatology provider will assess breathing, and at 30 seconds announce "breathing well", or "not breathing well" and the VFF will record this.

#### **Standard Arm**

- If the infant is randomized to the Standard 30-60 sec arm, the cord can be clamped at **30 sec if the infant is NOT breathing well**. The option to delay cord clamping, past 30 seconds but NOT longer than 60 seconds, if the infant is NOT breathing well is at the discretion of the OB and Neonatology teams. This option is consistent with the current ACOG

guideline of allowing 30-60 seconds of DCC for preterm infants. **If the infant is breathing well, the cord is clamped at 60 sec.** Heart rate will be checked at 50 seconds prior to cord clamping at 60 seconds. The infant is then moved to the resuscitation area for ventilatory assistance, either CPAP if breathing well or PPV if not, per NRP guidelines (see below).

- If the infant is designated as breathing well at 30 seconds but stops breathing prior to 60 seconds, the cord may be clamped prior to 60 seconds at the discretion of the OB and Neonatology providers.
- Although some obstetricians and neonatologists have advocated that the umbilical cord be “milked”, as an alternative to delayed cord clamping, umbilical cord milking is not an approved part of the intervention in either standard or VentFirst arms. If the cord is milked prior to clamping, this will be noted on the DR Script and would be considered a protocol deviation. Umbilical cord milking is not recommended as a standard practice in national and international guidelines.

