### **Post-Delivery Instructions and Data Collection (both arms)**

#### **Infant (neonatology team):**

- Number of seconds after birth that the cord was actually clamped is recorded by the VFF. For quality control purposes, audio recording of the DR intervention may be performed for later review by the site CRC or PI to validate data written on DR script.
- If the cord was clamped more than +/- 15 seconds from the target time required in the specific study arm (30-60, or 120 sec), the VFF will record a reason on the delivery data sheet and a protocol deviation will be reported (see section 10.2.2).
- After the baby is moved to the resuscitation table, further resuscitation measures are carried out per NRP guidelines.

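### The deviation window for Standard-arm clamping ignores the breathing call, so an early clamp of a breathing-well control can go unreported

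*Protocol*

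**What the plan says.** Protocol section 4, Standard Arm, gives two rules according to the breathing call at 30 s.

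- Not breathing well: the cord can be clamped at 30 s. "The option to delay cord clamping, past 30 seconds but NOT longer than 60 seconds, if the infant is NOT breathing well" is left to the obstetric and neonatal teams.
- Breathing well: "If the infant is breathing well, the cord is clamped at 60 sec". The one exception specific to this arm is an infant called breathing well at 30 s who then "stops breathing prior to 60 seconds, the cord may be clamped prior to 60 seconds at the discretion of the OB and Neonatology providers".

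Two other places in section 4 say when a clamp time counts as off target.

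- Delivery Preparation: the facilitator records a reason "if the time is more than 15 seconds shorter or longer than the assigned time". The assigned time is not defined by breathing call.
- Post-Delivery Instructions and Data Collection: a reason is recorded and a protocol deviation reported if the clamp was "more than +/- 15 seconds from the target time required in the specific study arm (30-60, or 120 sec"). This gives one target for the whole Standard arm.

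The same post-delivery section has the facilitator record the actual clamp time in seconds. Section 7 (Per Protocol population) removes infants with intervention non-adherence from the sensitivity analyses.

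**The concern.** The instruction to the delivery team is split by breathing call, but the rule that checks adherence to it is not. For an infant not breathing well, an arm-level target of 30-60 s matches the discretion that the protocol gives. For an infant breathing well, it is wider than the instruction, because the Standard Arm text names a single time.

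Cohort 2 consists of the infants breathing well. If its controls can be clamped well short of the stated time without a recorded reason or a reported deviation, the trial's own account of adherence in that cohort will look better than it was. A per-protocol set built on reported deviations would then keep controls who did not receive the Standard-arm instruction for their breathing call.

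**Working it through.** **The plan's own figure.** The nearest stated result is the cohort 2 power of about 81% (298 per arm, odds ratio 0.59, two-sided 5%, section 7, Study Size Considerations). It is checked here to see whether anything in it depends on the deviation window. The control failure rates are 0.551 (share 0.38) and 0.256 (share 0.62).

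- VentFirst failure rate in each stratum: q = OR·p / (1 − p + OR·p), giving 0.420 and 0.169.
- Infants per arm in each stratum: m = 298 × 0.38 = 113.24 and 298 × 0.62 = 184.76.
- D = Σ (m/2)(p − q) = 7.42 + 8.06 = 15.48.
- Null variance, with p̄ the mean of p and q: V0 = Σ (m/2) p̄(1 − p̄) = 14.1 + 15.5 = 29.6.
- Alternative variance: V1 = Σ (m/4)[p(1 − p) + q(1 − q)] = 13.9 + 15.3 = 29.2.
- Power = Φ[(15.48 − 1.96 × √29.6) / √29.2] = Φ(0.89), about 81.4%.

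The stated 81% reproduces, and no deviation window enters the calculation.

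**The windows.** The tolerance is 15 s on either side, and only a clamp beyond it is flagged.

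| Infant | Target used | Arithmetic | Not flagged |
|---|---|---|---|
| Standard, breathing well | arm-level 30-60 s (post-delivery rule) | 30 − 15 to 60 + 15 | 15-75 s |
| Standard, breathing well | 60 s (Standard Arm text) | 60 − 15 to 60 + 15 | 45-75 s |
| Standard, not breathing well | 30 s with discretion to 60 s | 30 − 15 to 60 + 15 | 15-75 s |
| VentFirst, either call | 120 s | 120 − 15 to 120 + 15 | 105-135 s |

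**The gap.** For a breathing-well control, the first two rows differ from 15 s to just under 45 s. Three examples, each measured against 60 s:

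- clamped at 44 s: 60 − 44 = 16 s short, just beyond the tolerance;
- clamped at 30 s: 60 − 30 = 30 s short, twice the tolerance;
- clamped at 15 s: 60 − 15 = 45 s short, three times the tolerance.

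None of these is a reportable deviation under the post-delivery rule as worded. Under the Delivery Preparation rule, each needs a recorded reason only if the assigned time is read as 60 s, and the text does not say so.

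**Unequal strictness within cohort 2.** The unflagged window is 75 − 15 = 60 s wide for controls and 135 − 105 = 30 s wide for VentFirst infants. With a 60 s target for controls it would be 75 − 45 = 30 s in both arms. For infants not breathing well, the arm-level rule and the Standard Arm text give the same window, so the gap is confined to cohort 2 controls.

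**The case against.** The best defence is that the protocol read as a whole is clear enough. The Standard Arm section is the operative instruction. The assigned time is most naturally the time that section assigns. Section 10 requires the study to be conducted as described and treats unplanned variances as deviations or violations. The facilitator also reads from a script held in the Manual of Procedures, which may state the 60 s target. Some of this stands: a careful site could reach the 45-75 s window. But the post-delivery rule is the only one that puts a number on a reportable clamp-time deviation, and it spells out its target as 30-60 s for the arm. A site applying it literally would report nothing.

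A reader might infer more than the documents support.

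- *That the cohort 2 control is not fixed.* It is: the Standard Arm text names 60 s and one arm-specific exception.
- *That hypothesis 2 contradicts it.* Section 2.1 describes the comparator with "compared to those with cords clamped at 30-60 seconds, followed by assisted ventilation" for both cohorts. That is the arm's label, and 60 s lies within it. It is less specific, not inconsistent.
- *That the conclusions in section 2.2 contradict it.* The row for hypothesis 1 alone begins "All EPT infants should have DCC for at least 30 seconds, and if the infant is" and goes on to infants not breathing. This is a floor for a guideline, which 60 s satisfies, and it does not define the comparator. Where both hypotheses are refuted, the floor is attributed to earlier studies.
- *That early clamping would be invisible.* The seconds are recorded for every infant. Only the flag is missing.
- *That the cohort 2 result would be biased by a calculable amount.* The protocol gives no effect of 30 s against 60 s. Its meta-analysis odds ratio of 0.59 compares delays of 30 s or more with immediate clamping, so both times fall on the delayed side. Any bias figure would need an assumed dose-response and an assumed rate of early clamping.

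**Conclusion.** The point holds in a narrow form and is minor. The Standard Arm text and the deviation rule use different targets for a breathing-well control, and the undefined assigned time does not settle which applies. On the literal reading, clamps from 15 s to just under 45 s in infants still breathing well are more than 15 s short of the stated time but are not reportable.

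The consequence is limited to which cohort 2 control deliveries need a recorded reason, are reported as deviations, and can be treated as non-adherent in the per-protocol analyses. The last of these assumes that non-adherence is taken from the deviation rule. The protocol does not say so, and the statistical analysis plan, which is not at hand, may define it otherwise. The intent-to-treat primary analysis, the sample size and the power do not change. How many deliveries would fall in the gap cannot be judged from the protocol.

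**What to change.** Reconcile the Standard Arm, Delivery Preparation and Post-Delivery Instructions text in section 4.

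- State the Standard-arm deviation target separately for each breathing call, and define the assigned time as that target.
- Carry the exception for an infant who stops breathing before 60 s into the deviation rule, so that a permitted early clamp is not counted as a deviation.
- Report the recorded clamp time by arm within cohort, so that adherence can be seen whatever the flag says.

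Which target applies to each breathing call is for the sponsor's clinicians. The cost is wording in the protocol and, where needed, the delivery script. Clamp time and breathing call are already collected. The one downside is that some control deliveries would become reportable deviations.
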